## Results

3

Among 37,775 participants, aged between 40 and 63 years, who received a health checkup between April and June in 2018, we have enrolled 1,692 CKD participants (4.5%). The selection process of study participants during this period is summarized in Fig. 2. Then we randomized 677 participants into the usual letter group, 677 participants into the nudge-based letter group, and 338 participants into the control group. We confirmed that a large number of eligible participants for the trial could be identified by routinely collected health checkup data. Table 3 shows participant characteristics in each group. Middle-aged men are the focus of our study participants. Age, eGFR, proportion of patients with urine protein ≥1+, blood pressure, and HbA1c level were similar between the groups. The proportion of patients with a previous visit was slightly higher in the control group than in the intervention group (no statistical test). We will continue to select eligible participants by the end of March 2019 and follow them until their health check-up at 2 years later.

**Fig. 2 fig2:**
[figure not shown]
**Selection process of study participants, from 2018 April to 2018 June.** Among 37,775 participants, aged between 40 and 63 years, who received a health checkup between April and June in 2018, we have enrolled 1,692 CKD participants (4.5%). CKD, chronic kidney disease; eGFR, estimated glomerular filtration rate; ESRD, end stage renal disease.

**Table 3 tbl3:** Participant characteristics.

	Control group (N = 338)	Usual letter group (N = 677)	Nudge-based letter group (N = 677)
Age, mean (SD), years	53.7 (6.6)	53.8 (6.5)	53.6 (6.6)
Male sex, n (%)	313 (92.6)	617 (91.1)	623 (92.0)
eGFR, mean (SD), mL/min/1.73 m^2^	68.7 (15.2)	68.1 (16.0)	68.7 (15.9)
Urine protein ≥+, n (%)	214 (63.3)	429 (63.4)	429 (63.4)
SBP, mean (SD), mmHg	129.8 (17.9)	129.9 (18.7)	130.2 (18.7)
DBP, mean (SD), mmHg	81.9 (13.0)	82.2 (12.9)	82.0 (13.0)
HbA1c, mean (SD), %	6.1 (1.1)	6.0 (1.1)	6.10 (1.22)
Hypertension, n (%)	138 (37.2)	252 (40.8)	264 (39.0)
Diabetes, n (%)	66 (19.5)	100 (14.8)	108 (16.0)
Current smoking, n (%)	120 (35.5)	217 (32.1)	229 (33.8)
Previous visiting,^a^ n (%)	19 (5.6)	31 (4.6)	28 (4.1)

SD, standard deviation; eGFR, estimated glomerular filtration rate; SBP, systolic blood pressure.

DBP, diastolic blood pressure; HbA1c, glycated hemoglobin A1c; CKD, chronic kidney disease.

a Previous visiting was defined as proportion of visiting to physicians within 6 months before health checkup.

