In the usual letter, we provide information about CKD based on clinical evidence; recommend visits to physicians; and show patients' individual health checkup results of the eGFR, urine protein, and risk factors of hypertension (systolic blood pressure/diastolic blood pressure ≥140/90 mmHg or receiving antihypertensive drugs), diabetes (glycated hemoglobin A1c level ≥6.5% or receiving antidiabetic drugs), and smoking (current smoker or not). In the nudge-based letter, we encourage visits to physicians using the nudge approach in behavioral economics. The nudge is defined as “any aspect of the choice architecture that alters people's behavior in a predictable way without forbidding any options or significantly changing their economic incentives” [9]. In general, behavioral economics researchers consider people's seemingly irrational behaviors, procrastination [14] and loss avoidance [15], to construct a nudge-based intervention. In this study, to alter the participant's visiting behavior to physicians in a clinically desirable way without forbidding any other options, our nudge approach includes “commitment” (designing the space for intentions prompts, where participants write the visiting date and time, solidifying their intention of visiting physicians, and preventing the procrastination) [16] and “loss-framed message” (considering loss avoidance and giving information that emphasizes the loss of opportunity for preventing CKD progression and for work) [17]. We also add information about the concrete steps to visit a physician in order to decrease the participant's burden (cognitive costs). We also show individual health checkup results in the nudge-based letter as in the usual letter. The volumes of documents are similar between both the nudge-based letter and usual letter. Supplemental Fig. 1 and Supplemental Fig. 2 show the format of these letters. These letters will be sent by mail to individuals from the health insurance association. The research team is not involved in the individual shipping business of personal data, and the trial is open-labeled without blinding because it would be difficult to send a placebo letter to the control group.

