**Secondary outcome**
**Change in the eGFR** Change in the eGFR (mL/min/1.73 m^2^) from the pre-intervention value to the post-intervention value after 2 years
**Proportion of continuous visiting** The proportion of participants who visit physicians for CKD care at least twice between 1 year and 2 years after the intervention

CKD, chronic kidney disease; eGFR, estimated glomerular filtration rate.

The medical claims data from the intervention date to 6 months after the intervention is used to define visiting behavior. If the participants have CKD-related diagnostic codes (Table 2) in their medical claims during this period, it is considered that they visited physicians for CKD care. The health checkup data of pre-intervention and post-intervention (2 years later) is used to define change in the eGFR.

**Table 2 tbl2:** Chronic kidney disease-related diagnostic codes.

	ICD-10 codes
Chronic kidney disease	N170, N171, N172, N178, N179, N180, N188, N189, N19, N990
Tubulointerstitial nephritis	N110, N111, N118, N119, N12, N140, N141, N142, N143, N144, N150
Chronic glomerular nephritis	N002, N003, N004, N006, N007, N009, N012, N014, N016, N017, N019, N028, N029, N030, N032, N033, N034, N036, N037, N039, N040, N042, N044, N046, N049, N050, N051, N052, N053, N054, N055, N056, N057, N058, N059, N069, N079, N085
Diabetic nephropathy	E102, E112, E132, E142
Hypertensive nephrosclerosis	I129, I120
Polycystic kidney disease	Q613

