#### Data analysis

2.6.2

We will describe participant characteristics with means and proportions by groups and compare them between groups using analysis of variance and chi-square tests, and their non-parametric analogs, as appropriate.

In our analysis to evaluate the effect of the intervention, we will conduct an intention-to-treat analysis. In our primary analysis, we will apply a logistic regression model with a dichotomous variable of visiting behavior as the dependent variable, and dummy variables of three groups and allocation adjustment factors (quarterly timing of the intervention, eGFR, and urine protein) as the independent variables. In the logistic regression model, we will estimate p-values by omnibus tests (Wald test) for the differences in outcome (proportion of visits to physicians) between the groups. If the two-sided p-values by omnibus tests is <5%, we will conclude that there are statistically significant differences in outcome between the groups and will continue to perform pairwise comparisons in order to adjust for multiple comparisons [18]. From the logistic regression model, we will estimate risk differences and their 95% confidence intervals using the model-based standardization technique [19]. In a sensitivity analysis, we will adjust for the presence of lifestyle guidance involved in the usual follow-up after the health checkup. We will also estimate the proportion and its Wald-type 95% confidence interval of the primary outcome for each group. Further, we will estimate the odds ratio and its 95% confidence intervals, and compare them between the groups.

For the confirmatory analysis of the secondary outcome, we will apply the closed testing procedure. Specifically, only if the two-sided p-values by the omnibus test of the primary outcome are <5%, we will conduct the following analysis on the difference of the eGFR. We will apply a linear regression model with the difference of the eGFR as the dependent variable, and dummy variables of the three groups and allocation adjustment factors (quarterly timing of the intervention, eGFR, and urine protein) as the independent variables. We will estimate p-values by omnibus tests (Wald test) to determine differences in outcome (i.e., the difference of eGFR) between the groups. If the two-sided p-values by omnibus tests are <5%, we will conclude that there are statistically significant differences in outcome between the groups and will continue to conduct pairwise comparisons.

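### Table 3 exchanges the hypertension percentages of the control and usual letter groups; separately, baseline hypertension and diabetes are worth pre-specifying as prognostic covariates in both outcome models

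*Protocol article*

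**What the plan says.** Section 3 (Results), Table 3 describes the 1,692 participants screened from April to June 2018, under the column heads "Control group (N = 338)", "Usual letter group (N = 677)" and "Nudge-based letter group (N = 677)". The hypertension row reads "Hypertension, n (%) 138 (37.2) 252 (40.8) 264 (39.0)".

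The text of section 3 calls mean blood pressure and HbA1c similar and reports that previous visiting was slightly higher in control. It does not comment on the prevalence of hypertension or diabetes.

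Section 2.3 defines both conditions when it describes the letter's content: hypertension as "systolic blood pressure/diastolic blood pressure ≥140/90 mmHg or receiving antihypertensive drugs" and "diabetes (glycated hemoglobin A1c level ≥6.5% or receiving antidiabetic drugs)".

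Section 2.5 counts a participant as having visited if a code from Table 2 appears within six months. Besides CKD itself, Table 2 lists "Diabetic nephropathy" and hypertensive nephrosclerosis.

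Section 2.6.2 gives the covariates of the primary logistic model as "dummy variables of three groups and allocation adjustment factors (quarterly timing of the intervention, eGFR, and urine protein) as the independent variables". The eGFR linear model has the same set. Diabetes appears elsewhere only as a subgroup factor.

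**The concern.** There are two separate matters.

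**The table.** With 2:2:1 allocation the raw counts cannot be compared by eye, so a reader uses the percentages. As printed, control looks like the least hypertensive group; by its own count it is the most hypertensive. The error reverses the order in a baseline table whose purpose is to show comparability.

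**The models.** The primary outcome is any Table 2 code, and two of the code families are renal complications of diabetes and hypertension. People with these conditions at baseline therefore plausibly have a different chance of a counted visit, whichever group they are in. For eGFR change, the plan's own letter presents both conditions as risk factors. A model restricted to the allocation factors leaves this information unused. What is at stake is precision, and protection against whatever chance imbalance remains at the end of enrolment. The validity of the comparison is not at stake.

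**Working it through.** **1. Reproducing Table 3.** Inputs are the printed counts and group sizes (338, 677, 677); percentage = 100 × n/N.

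- Of the 18 cells that give a count and a percentage, 16 reproduce to 0.1 point.
- Hypertension, control: 138/338 = 40.83%, printed 37.2.
- Hypertension, usual letter: 252/677 = 37.22%, printed 40.8.
- Hypertension, nudge-based letter: 264/677 = 39.00%, printed 39.0.

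Each failing cell carries exactly the other group's percentage.

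**2. Other explanations.**

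- Different denominators: 138/0.372 = 371 and 252/0.408 = 618. Neither is a group size.
- Wrong count in control: 125/338 = 37.0% and 126/338 = 37.3%, so no whole number out of 338 gives 37.2%.
- Wrong count in usual letter: 276/677 = 40.8% would fit that cell taken alone, but it would leave the control cell unexplained.

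An exchange of the two percentages is the simplest reading. Source data should confirm it.

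**3. Size of the differences** (control / usual / nudge; Pearson chi-square, no continuity correction).

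- Hypertension, by count: 40.8 / 37.2 / 39.0%. Control minus both letter groups: 138/338 − 516/1354 = 2.7 points, p = 0.36. Three-group p = 0.52.
- Diabetes: 19.5 / 14.8 / 16.0%. Control minus both letter groups: 66/338 − 208/1354 = 4.2 points, p = 0.06. Three-group p = 0.15. The most extreme pair, control versus usual letter, has p = 0.054.

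**4. How common the two covariates are.** Hypertension: (138 + 252 + 264)/1692 = 38.7%. Diabetes: (66 + 100 + 108)/1692 = 16.2%. Previous visiting: (19 + 31 + 28)/1692 = 4.6%. The printed diabetes percentages and the corrected hypertension percentages use the full group sizes, so both variables appear to be held for everyone.

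**5. Illustration of a chance shift in this sample.** Assumption, not in the document: having the condition raises the probability of a counted visit by 5 to 30 points. Shift in control relative to the letter groups = prevalence difference × assumed effect.

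- Hypertension: 2.72 × 0.05 = 0.14 to 2.72 × 0.30 = 0.82 points.
- Diabetes: 4.16 × 0.05 = 0.21 to 4.16 × 0.30 = 1.25 points.

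The planned differences from control are 5 and 10 points (section 2.6.1). A shift in this direction would dilute the letter effect.

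The upper end is doubtful. Effects of 30 points for diabetes and 10 for hypertension would by themselves give 0.195 × 0.30 + 0.408 × 0.10 = 9.9% visiting in control, against 5.6% with any previous visit in Table 3. New coding after the checkup could account for some of the gap, but the document gives no figure for it.

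**6. Does any design figure depend on the row?** No. With 850, 1700 and 1700 participants and proportions of 0.15, 0.20 and 0.25, pairwise power is about 88% (control v usual), over 99.9% (control v nudge) and 94% (usual v nudge). All tests succeed jointly in 81.6% of 200,000 simulated trials. The stated minimum of 80% is met and does not involve Table 3.

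**The case against.** The strongest case against is that the first part is clerical and the second is a preference. Most of the supporting argument stands.

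- **A reader might infer that the swap hides more disease under care in control.** The document does not support this. The counts stand beside the wrong percentages, the higher diabetes percentage in control is printed correctly, and the text itself reports the higher previous visiting. The statement about blood pressure and HbA1c is true of the means. The section 2.3 definitions also accept a raised measurement without treatment, so they do not identify people already seeing a physician; the treated share is not given. That Table 3 uses those definitions is itself an inference.
- **A reader might infer that the planned analysis is biased against the letters.** It is not. Allocation is randomised and the model contains the stratification factors. The differences fit chance and cover only the first enrolment quarter, with enrolment continuing to March 2019. The shifts in the working are conditional on this sample and on assumed effects.
- **Choosing covariates because they differ between groups would be data-driven.** This is correct, so the case for them must rest on prognosis alone.
- **The route from comorbidity to outcome code is uncertain.** Table 2 does not count plain diabetes or hypertension. The limitations in section 4 raise the reverse possibility, that patients with hypertension receive CKD care without a counted code. This weakens the hypertension route; the diabetes route is not discussed there.

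What remains is that both variables are plausible predictors, already collected, and unused in the two models. The argument is weaker for eGFR change than for visits, since it rests only on the plan's description of them as risk factors.

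**Conclusion.** The exchange of the two percentages is established from Table 3 alone: 3.6 points in each of two cells (40.8 − 37.2), enough to reverse the order of control and usual letter. It is a reporting error with no consequence for the design or the planned tests.

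The covariate point holds as a recommendation and is not an error in the plan. The analysis with allocation factors only is valid. Adding baseline hypertension and diabetes would be expected to improve precision and limit the effect of chance imbalance, provided they do predict the outcome. The document gives no association between either condition and the outcome, so the gain cannot be sized.

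**What to change.** 1. Check the hypertension row of Table 3 against source data. If the counts are right, print control as 138 (40.8) and usual letter as 252 (37.2). Where section 3 discusses balance, give the hypertension and diabetes percentages alongside the means.
2. Before outcome data are seen, add baseline hypertension and diabetes to the logistic model for visiting and to the linear model for eGFR change. State the definitions used and give prognosis as the reason, not the first-quarter differences.
3. Keep the model-standardised risk difference as the estimate for the primary outcome, so that the target does not change with the covariates. The secondary odds ratio does depend on the covariate set, so report which model it comes from.

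The cost is one table correction and two extra model terms, with no new data collection. If outcome data have already been seen, present the extended models as a sensitivity analysis and leave the primary model as it is.

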## Discussion

4

Large-scale CKD screening is criticized from the viewpoint of cost-effectiveness [20], but consensus has been obtained that the prevention of CKD progression is an important public health issue. Because Japan is a country where pre-diagnosis CKD data have been accumulated by nationwide health checkups, we could develop an efficient intervention after CKD screening and assess its effectiveness in the real world. Conventional CKD screening in Japan can detect potential CKD patients from the general population but lacks intervention to make them visit physicians after the screening. Consequently, we designed a pragmatic trial of nudging CKD patients to visit physicians after screening. The results from this trial will contribute to filling the gap between screening and subsequent medical interventions and will also be a model for a “learning health system” that utilize the routinely collected health data to improve the health care system.

Our pragmatic RCT is designed in the health care system. By taking advantage of having large-scale health checkup data in Japan, we are conducting this implementation research to improve patients' visiting behaviors to physicians after CKD screening. Since it is usually difficult to allocate intervention, i.e., whether to provide medical treatment, in a high-risk population, our intervention to encourage patients to visit physicians by just sending them a letter is a feasible and realistic approach for the prevention of CKD progression. Our intervention is inexpensive and can be implemented for other health issues in the future. We will only use routinely collected data from the health care system to identify eligible participants, follow them, and measure their outcomes. This makes it possible to perform a large-scale pragmatic RCT involving a wider population at a lower cost. Our pragmatic RCT can assess both short-term outcomes of patients’ visiting behavior and long-term outcome of renal function through analysis plans, in which we can manage statistical multiplicity.

Another major feature of this trial is to examine the effect of a nudge approach on patients' behaviors in one important issue of public health. Many of the interventional studies in public health have focused on the effect of mandatory interventions (restricting a patient's choice) or financial incentives. Additionally, these studies have been conducted on some limited issues, including smoking and obesity. In behavioral economics, an increasing number of studies has investigated the effect of the nudge approach, especially in the United States and Europe [16,[21], [22], [23]]. However, many of these studies have also focused on smoking and obesity, or when studying the other clinical issues, the study subjects have usually been limited to patients in a certain hospital. Therefore, the present trial is unique in that it is investigating the effect of the nudge approach in Japan, an unexamined clinical issue, and evaluating subjects from a wider range of regions.

Investigating the effect of the nudge approach is recommended by the Japanese government, which followed the Behavioral Insights Team in the United Kingdom and founded the Behavioral Sciences Team in 2017, to apply behavioral economics and nudge in various policy fields, including health policy. As we explained earlier, we considered patients’ behavioral characteristics and designed the letter accordingly. Thus, our nudge approach can be expected to be cost-effective.

There are several limitations to this pragmatic RCT. First, we will use only routinely collected data. Avoiding additional data collection dramatically decreases the cost and effort, and enables such a large-scale pragmatic RCT to be conducted. However, we cannot assess unmeasured factors, which are not included in the health checkup and medical claims. Second, we will use a one-time measurement of kidney function to identify CKD participants at screening. The original definition of CKD is a continuous renal function deficiency, which needs at least two time measurements of kidney function [24,25]. In previous clinical studies, a one-time measurement of kidney function is often used to define CKD, which is validated as a risk factor in identifying the population with renal risk [26,27]. Further, our intervention to encourage potential CKD participants to visit physicians is clinically reasonable to confirm the presence of CKD by performing re-tests of kidney function. Third, we will define our outcomes of visiting behavior by CKD-related diagnostic codes in medical claims data, and thus, patients who receive CKD care without CKD-related diagnostic codes will be misclassified. For example, CKD patients with hypertension might receive CKD care without CKD-related diagnostic codes. However, we expect this misclassification to be a non-difference between allocation groups, and the effect of the intervention will not be biased by this factor. Fourth, the trial is open-labeled without blinding. However, because we will use routinely collected data to measure study outcomes based on a pre-specified definition, outcome assessment will be less susceptible to non-blinding. Fifth, some participants are excluded because of the absence of CKD screening. In Fig. 2 and 92.3% of participants received CKD screening. Whether a participant receives CKD screening in addition to the mandatory health checkup items is decided by each company and cannot be decided by the individual participant. Therefore, the effect of excluding a small portion of participants without CKD screening is limited. Finally, we will include the middle-aged male-focused Japanese population in this trial. Although this pragmatic RCT in the health care system will include a broader population than a conventional trial, generalizability to other populations is limited.

## Conclusions

5

With prevalence of 4.5% for CKD and only 7–8% for visiting physicians before screening, it is apparent that the patients who are not under the care of a physician continue to have deteriorating kidney function. We anticipate that with an increase in the proportion of patients visiting physicians following screening, clinical management will be instituted in time and patient outcomes optimized. This will also ensure returns on investment in CKD screening programs. The intervention we will examine is a low-cost method that can be implemented to other health issues in the future. The trial will also show the model for utilizing routinely collected data to assess the effect of a public health intervention in the real world.

